## Abstract

**Background:**

Traditional exercise [supervised exercise (SE)] intervention has been proved to be one of the most effective ways to improve metabolic health. However, most exercise interventions were on a high-cost and small scale, moreover lacking of the long-term effect due to low engagement. On the other hand, it was noteworthy that gamification and social incentives were promising strategies to increase engagement and sustain exercise interventions effects; as well as mobile technologies such as WeChat also can provide an appropriate platform to deploy interventions on a broader, low-cost scale. Thus, we aim to develop a novel exercise intervention (‘S&G exercise intervention’) that combines SE intervention with gamification and social incentives design through WeChat, with the aim of improving metabolic health and poor behaviors among overweight and obesity children.

**Methods:**

We propose a randomized controlled trial of a ‘S&G exercise intervention’ among 420 overweight and obese children who have at least one marker of metabolic syndrome. Children will be randomized to control or intervention group in a 1:1 ratio. The exercise intervention package includes intervention designs based on integrated social incentives and gamification theory, involving targeted essential volume and intensity of activity (skipping rope) as well as monitoring daily information and providing health advice by WeChat. Participants will undertake assessments at baseline, at end of intervention period, in the follow-up time at months 3,6,12. The primary outcome is outcome of metabolic health. Secondary outcomes include behavioral (e.g., diary physical activity, diet) and anthropometric measures (e.g., body fat rate and muscle mass).

**Discussions:**

This will be the first study to design an exercise intervention model that combines traditional supervised exercise (SE) intervention with gamification and social incentives theory through WeChat. We believed that this study could explore a low-cost, easy-to-popularize, and effective exercise intervention model for improving metabolic health and promote healthy among obese children. Furthermore, it will also provide important evidence for guidelines to prevent and improve metabolic health and health behaviors.

**Trial registration:**

10-04-2019;Registration number: ChiCTR1900022396.

## Background

Childhood obesity is correlated with cardiovascular disease (CVD) and type 2 diabetes in adulthood [1–3]. The worldwide prevalence of childhood obesity has been steadily increasing in the past decades [4, 5]. China has now joined this world epidemic, a recent survey suggested that mean prevalence of overweight and obesity increased from 5.3% (5.2–5.4) in 1995 to 20.5% (20.4–20.7) in 2014 [6]. Moreover, a Chinese study reported that in 2010–2015, the age-adjusted prevalence of overweight and obesity among boys increased from 21.2 to 31.7% and from 10.6 to 16.9% among girls [7]. It has been proved that obese children are more likely to have metabolic diseases than his/her non-obese peers [8]. Indeed, up to 90% of overweight adolescents had at least one marker of metabolic syndrome and 56% had two markers [3]. Moreover, the risk of metabolic diseases in adults is formed from childhood [9], and some studies has demonstrated that metabolic abnormality in childhood obesity may be a significant predictor to CVD and other chronic diseases in adulthood [10, 11]. Therefore, it is important for obese children to improve metabolic health in early childhood.

There is strong evidence that exercise, especially traditional supervised exercise (SE), is one of the effective ways to improve metabolic disease risk factors [12, 13]. As the traditional supervised exercise (SE) ensure intensity and dose of physical activity. Indeed, the importance of activity intensity and dose has been also emphasized in several systematic reviews [13–15].

A systematic review has found that only moderate and high intensity exercise can improve health outcomes such as obesity and elevated blood glucose level, rather than low intensity exercise [16]. Therefore, it has even been demonstrated that SE interventions is even more effective than daily physical activity (PA) intervention in improving outcomes including metabolic biomarkers [16]. However, previous SE intervention was mainly supervised by health professionals, resulting in high cost and difficult to translate into large scale [16–18]. In addition, most SE interventions are lack of motivation and interest, because it specified repetitive exercise content or form. Which also makes it difficult for participants to develop the exercise habit and keep on when the intervention stopped, so that the long-term effect of interventions is questionable [19, 20].

The rapidly expanding availability of mobile technologies such as wearable devices and smartphones makes up limitations above and provides an opportunity to deploy interventions on a broader, low-cost scale [21]. In particularly, WeChat (the Chinese version is Weixin), as a representative form of modern messaging software, reaching 1058 million active users, has been used to healthy behavior modifications and already shown potential impacts [22, 23]. It has been demonstrated that using the WeChat app for follow-up visit was time-effective, cost-effective, and convenient [24].

Besides, latest researches have highlighted two features important for behavior change: (i) Social Incentive; (ii) Gamification. Social incentives, or the influences that motivate individuals to adjust their behaviors based on social networks, is ubiquitous and is an effective way to increase engagement and stimulate the long-term health behavior changes [21, 25]. There is a recent call for studies on the potential uses of social engagement strategies in promoting health published by the New England Journal of Medicine [25]. The latest randomized systematic review also suggested that the intervention group with increased social incentives such as peer support and mutual encouragement was more significant change than the control group in healthy behaviors [26].

Additionally, gamification, the application of game design elements such as points and levels in non-game contexts, in order to enhance the interest of context, is increasingly being used to promote changes in healthy behaviors, especially PA [21, 27]. A randomized controlled trial published in JAMA Internal Medicine tested the effectiveness of gamification-based design in improving and maintaining healthy behavior [28]. Besides, gamification-based design not only improve the healthy behaviors after intervention, it has also a positive effect on long-term maintenance.

Social incentives in combination with gamification interventions can make up the limitation of SE intervention. However, so far little research has done to combine SE intervention with gamification and social incentives to improve metabolic health.

Therefore, we propose a randomized controlled trial of a ‘S&G exercise intervention package’ among obese and overweight children. The intervention package includes intervention designs based on integrated social incentives and gamification theory, involving targeted essential volume and intensity of activity (skipping rope) as well as monitoring daily information and providing healthy advice by WeChat.

The aims of this study are twofold. First, the randomized controlled trial targeted obese and overweight children, is to assess the effectiveness of a ‘S&G exercise intervention’ to improve metabolic health. The second aim is to test the effect of this innovative exercise intervention on healthy behaviors changes such as PA, diet, sleep health and screen media use, which are significantly associated with healthy behaviors and health status in their adulthood. We hypothesize that the intervention will improve metabolic health and unhealthy behaviors in obese children. Furthermore, it will make a significant contribution to childhood health research and practice by developing a novel intervention model to promote metabolic health and healthy behaviors among obese children.

## Methods/design

### Study design

This protocol describes the setting of a 6-months intervention period and 12-months follow-up period assessing the impact of a ‘S&G exercise intervention package’ (targeted an intervention integrated social incentive theory and gamification theory with a smart phone app as support) on improving metabolic health in overweight and obese children. Participants were randomly assigned to either an intervention or a control group. The complete process is outlined in Fig. 1.

**Fig. 1 Fig1:**
[figure not shown]
Study design flow chart. *‘S&G exercise intervention package’* (deliver via WeChat and Actigraph wGT3X-BT;). Social incentive intervention: Divide the intervention group into 30 teams; Organize a kick-off meeting; Report daily information within Teams; Others: Peer support; Accountability; Team discussion. Gamification intervention: Members get points from different types of game activities; Use performance as punishment for members who fail to complete tasks; Rank, badge and reward according to points; Held a skipping competition online

### Ethics approval

The study protocol was approved by the Ethics Committee of Shanghai Jiaotong University School of Medicine (SJUPN- 201813). This research is supported by the National Natural Science Foundation of China (71804110).

### Sample size consideration

Based on the relative studies on exercise intervention with obese children [29], the sample size required for each group was estimated to be about 175 with a power of 80%, an α of 0.05, and assumed an effect size of 0.30. Therefore, a total of 350 children are need. To account for 20% loss-to-follow-up, a total of 420 children will be recruited.

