### Randomization

The study will use stratified random sampling, and the random sequence of primary schools will be computer generated. Specifically, it stratified by school district, grades and size in each center. All of the children in the selected primary schools of different grades were invited to participate in the study.

After both parents and children written informed consent have been obtained, it will be allocated into either an intervention or control group in a 1:1 ratio. Neither the study team nor the participant knew the group allocation prior to the start of the intervention program.

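### The 20% loss allowance was added to 350 rather than divided out, so 420 recruits leave 336 children, not the 350 said to be needed (minor arithmetic error)

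*Protocol article*

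**What the plan says.** The protocol article, under Sample size consideration, gives a short chain of figures.

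- Design inputs: "with a power of 80%, an α of 0.05, and assumed an effect size of 0.30".
- Size per group: "the sample size required for each group was estimated to be about 175".
- Total: "Therefore, a total of 350 children are need".
- Allowance for loss: "To account for 20% loss-to-follow-up, a total of 420 children will be recruited".

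The Methods part of the Abstract repeats the recruitment figure ("among 420 overweight and obese children"), and the Randomization section confirms equal allocation ("it will be allocated into either an intervention or control group in a 1:1 ratio"). No other section gives a different loss rate, inflation method or target number of children with outcome data.

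**The concern.** The section makes three linked statements: 350 children are needed, 20% may be lost, and 420 recruits cover that loss. They cannot all hold. A loss rate applies to the children recruited, so the number needed has to be divided by the fraction retained. Adding 20% to the number needed gives a smaller figure.

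What is at stake is whether the stated power and the stated attrition allowance are delivered together. Follow-up runs to 12 months after a six-month intervention, so readers will compare the number retained with 350. A trial that loses exactly the share it planned for would appear to have missed its own target.

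**Working it through.** **Inputs, all from Sample size consideration except the allocation ratio (Randomization):** power 80%; alpha 0.05; standardised effect size 0.30; about 175 per group; 350 in total; 20% loss; 420 recruited; 1:1 allocation. The article does not say whether alpha is one- or two-sided. I take two-sided, because it reproduces 175 per group, whereas one-sided gives 138. The choice affects the power figures but not the inflation step.

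**Step 1. Reproduce the base size.** For two means with equal groups:

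n per group = 2 × (z for 1 − α/2 + z for power)² / d² = 2 × (1.960 + 0.842)² / 0.30² ≈ 174.4, rounded up to 175.

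The t-test version gives 175.4. The stated 175 per group and 350 in total therefore reproduce.

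**Step 2. Reproduce the recruitment figure.**

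- Multiplying: 350 × (1 + 0.20) = 420. This matches the article exactly.
- Dividing: 350 / (1 − 0.20) = 437.5, rounded up to 438 (219 per group). This does not match; it is 18 more than 420.

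**Step 3. What 420 delivers at the stated loss.**

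- 420 × 0.80 = 336 children, or 168 per group.
- Shortfall: 350 − 336 = 14 children (14 / 350 = 4%).
- Largest loss that still leaves 350: 1 − 350/420 = 16.7%.

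**Step 4. Effect on power at effect size 0.30, two-sided alpha 0.05.**

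| Children per group | Normal approximation | t-test |
|---|---|---|
| 175 | 80.1% | 79.9% |
| 168 | 78.5% | 78.3% |

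On either method the drop is 1.6 percentage points. The effect detectable with 80% power at 168 per group is 0.307 (t-test) instead of 0.30.

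**The case against.** **The consequence is trivial.** Power falls by 1.6 points, the per-group size is given only as an approximation, and the effect size is a round assumption. This stands as an argument about importance, and it is why the point is minor. It does not remove the inconsistency: 168 per group is below even the unrounded 174.4, so rounding does not explain the gap.

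**336 is a worst case.** It assumes that a lost child contributes no outcome data. The article plans five assessments, and Statistical analyses specifies a linear mixed model with a random subject effect. A child lost after an earlier post-baseline visit still contributes to that model, and the article does not say at which visit the 20% applies. This partly stands. It does not help for children lost before the first post-baseline visit, and the sample size section derives its number from a plain two-group comparison and sets 350 as the number needed.

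**Baseline adjustment would absorb the shortfall.** A reader might infer this, but the documents do not support it. Statistical analyses lists time, treatment, their interaction and covariates found to be unbalanced; it does not list the baseline value as a covariate, and no baseline correlation r is given. With r as an assumption, the answer depends on the analysis. Under analysis of covariance the variance factor is 1 − r², the break-even is at r of about 0.21, and power at 168 per group is 84.9% at r = 0.4. If the interaction is instead read as a difference in change from baseline, the factor is 2(1 − r), and power at r = 0.4 is about 71%.

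**An article condenses the full protocol.** That excuses omissions. Here a stated figure does not follow from its stated inputs.

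**Conclusion.** The point holds as a minor arithmetic error. The allowance was applied as 350 × 1.2 instead of 350 / 0.8, so 420 recruits do not secure 350 children at a 20% loss. The size is 14 children short at follow-up, about 78.3% power instead of about 80%, and cover for a loss of 16.7% instead of 20%. The power figures assume a two-sided test, an unadjusted comparison of two equal groups, loss spread equally between them, and no outcome data from lost children.

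A reader might infer that the trial is materially underpowered, or that 18 more children must be recruited. Neither follows. The power loss is under 2 points, and correcting what the sentence claims is enough. Nor does this check show anything about losses from team clustering or from several primary outcomes; those are separate questions and add no weight here.

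**What to change.** Keep 420 and restate the sentence in Sample size consideration along these lines: for an unadjusted two-group comparison with effect size 0.30 and two-sided alpha 0.05, 420 children give about 78% power if 20% are lost, or about 80% power if no more than 16.7% are lost. The sponsor should confirm that alpha is two-sided when making the change. The 420 in the Abstract can stay.

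The cost is one rewritten sentence and a slightly less favourable stated power. No extra recruitment and no change to visits or design is needed.

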### Recruitment and consent

Participants will be recruited randomly from primary schools in Shanghai. We will send invitation letters to primary schools. Before confirming their participation in the study, the study team will arrange a briefing session with the representatives of both school and parent interesting in participating to outline the study protocol. After confirmation of their participation, a total of six schools will be randomly selected.

Eligible individuals, accompanied by their parents, will be provided with consent forms including blood sample collection and physical examination before participating in the study.

### Inclusion criteria

Children are eligible for the study participation if they meet the following inclusion criteria.overweight or obese: according to the China school age children and adolescents overweight and obese BMI screening standard published by the Working Group on Obesity in China (WGOC) (see Table 1) [30]abnormal metabolic indicators: having any one of the following indicators defined mainly according to the criteria of the International Diabetes Federation (IDF 2007) adapted for children and adolescents [31]fasting glucose (FG) ≥ 5.6 mmol/Lsystolic blood pressure (SBP) ≥ 130 mmHg and/or diastolic blood pressure (DBP) ≥ 85 mmHg or was diagnosed with hypertensionHDL-cholesterol < 1.03 mmol/L, HDL cholesterol (boy) < 1.03 mmol/L, HDL cholesterol (girl) < 1.29 mmol/Ltriglycerides (TG) ≥ 1.7 mmol/Lelevated HbA1c defined as 5.7–6.4% according to the 2010 American Diabetes Association (ADA) criteria [32]

### Exclusion criteria

Participants are excluded if they are already participating in an exercise program, have been told not to exercise by a physician, have secondary obesity or metabolic abnormalities caused by hypothyroidism, injury of hypothalamus and so on, take medication that affects metabolism within 3 months before intervention, or if there is reason that participation is unsafe or infeasible for the individual.

### Randomization

The study will use stratified random sampling, and the random sequence of primary schools will be computer generated. Specifically, it stratified by school district, grades and size in each center. All of the children in the selected primary schools of different grades were invited to participate in the study.

After both parents and children written informed consent have been obtained, it will be allocated into either an intervention or control group in a 1:1 ratio. Neither the study team nor the participant knew the group allocation prior to the start of the intervention program.

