### Statistical analyses

Descriptive statistics will be calculated using mean (SD) for continuous variables and n (%) for categorical variables. Differences will be compared using independent t-tests for continuous variables (e.g., blood sample outcomes) and Chi-squared tests for categorial variables (e.g., education and household income of parents). Linear mixed models will be used to test for group differences on the main outcome variables at follow-up visits, while subject ID will be random effect, the main effect include time, treatment group, and the interaction between time and treatment. We will include covariates that are not balanced between two groups into the model. Data will be entered and cleaned with EpiData 3.0, and managed and analyzed using SPSS 24.0 and SAS. Statistical significance will be set at *P* < 0.05.

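### The Randomization section blurs sampling of schools with allocation of children, and the outcome model leaves out school and grade

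*Protocol article*

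**What the plan says.** All references are to the protocol article.

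- **Randomization.** The section opens with stratified sampling and says that "the random sequence of primary schools will be computer generated". District, grade and school size are given as strata in the next sentence. After parents and children have consented, an unnamed 'it' is allocated 1:1.
- **Abstract, Methods.** "Children will be randomized to control or intervention group in a 1:1 ratio". The Study design section likewise says that participants were assigned to the arms.
- **Recruitment and consent.** "a total of six schools will be randomly selected".
- **Sample size consideration.** "the sample size required for each group was estimated to be about 175". The inputs given for this are 80% power, a 5% significance level and a standardised effect of 0.30. No intracluster correlation (ICC) or design effect is mentioned.
- **Statistical analyses.** In the linear mixed model "subject ID will be random effect", with time, group and their interaction as fixed effects. Covariates enter if the arms turn out unbalanced on them. School and the strata are not named.

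**The concern.** The unit of allocation decides whether the sample size and the model are valid, so the section headed Randomization should settle it. Read alone, that section could describe schools being randomised. The Abstract and the Study design section describe individuals. The strata also mix levels: district and size belong to schools, whereas grade divides the children within a school. The section does not say whether any of them also governs allocation to arms.

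The model raises a second, smaller matter. Children from six schools and several grades are likely to differ by school and grade. Leaving those factors out, or letting them in only when a balance check happens to flag them, gives up precision that is almost free. If allocation is stratified by either factor, leaving it out also makes the test slightly conservative.

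**Working it through.** **1. The plan's own figure.** Inputs from Sample size consideration: effect size 0.30 (taken with SD 1), α 0.05 (assumed two-sided), power 80%.

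n per group = 2 × (1.960 + 0.842)² / 0.30² = 2 × 7.85 / 0.09 ≈ 174.4, rounded up to 175.

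The stated figure is reproduced, and power at 175 per group is 80.1%. A one-sided test would need 138, which does not match. The calculation treats children as independent.

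**2. Which unit does the text support?**

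| Section | Points to |
|---|---|
| Abstract, Methods | children |
| Study design | participants |
| Randomization, sequence and strata | schools, in a sampling context |
| Randomization, allocation sentence | no unit named; follows individual consent |
| Recruitment and consent | six schools selected, that is, sampled |
| Sample size consideration | independent children |
| Social incentive intervention design | 30 teams of 6–7 (180–210 children) formed by BMI, age and sex, with school not mentioned |

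Every statement that names an allocated unit names individuals. Schools appear only as something selected.

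**3. Children allocated: effect of leaving out school and grade.** Let R² be the share of outcome variance that school and grade explain. The documents give no value, so I assume 0.01 to 0.10.

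Standard error ratio without and with the terms = 1/√(1 − R²). Power with the terms = Φ(0.30/√(1 − R²) × √(175/2) − 1.96).

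| R² (assumed) | Standard error ratio | Power with terms |
|---|---|---|
| 0 | 1.000 | 80.1% |
| 0.01 | 1.005 | 80.5% |
| 0.05 | 1.026 | 82.1% |
| 0.10 | 1.054 | 84.1% |

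For the last row: 0.30/√0.90 = 0.3162; 0.3162 × 9.354 = 2.958; 2.958 − 1.96 = 0.998; Φ(0.998) = 0.841.

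**4. Whole schools allocated: a conditional calculation only.** Assumptions that are not in the documents: three schools against three, equal school sizes, the ICC, and a t test on 6 − 2 = 4 df. Analysed children: 420 less 20% = 336, that is 168 per arm and m = 336/6 = 56 per school.

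Design effect DE = 1 + 55 × ICC. Noncentrality = 0.30/√(2 × DE/168). Type I error of the planned subject-only model ≈ 2 × [1 − Φ(1.96/√DE)].

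| ICC (assumed) | DE | Power, 4-df test | Type I error, planned model |
|---|---|---|---|
| 0 | 1.00 | 55% | 5% |
| 0.01 | 1.55 | 39% | 12% |
| 0.02 | 2.10 | 31% | 18% |
| 0.05 | 3.75 | 20% | 31% |
| 0.10 | 6.50 | 13% | 44% |

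The last two columns describe different analyses. The power column is for a 4-df test that respects the schools, which the article does not contain. The type I error column is for the model it does contain. With a normal reference in place of 4 df, power at ICC 0.01 to 0.05 would be 60% to 30%, so much of the loss comes from having only six units.

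**The case against.** A reader might infer that this is a cluster trial with 20–39% power in place of 80%. The documents do not support that. No passage assigns schools to arms, and the balance in step 2 is towards children. The low figures also rest on a three-against-three split, an ICC and a 4-df test that appear nowhere in the article.

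A reader might also hold that strata missing from the model are an analysis error. As written they are sampling strata, and a treatment comparison need not adjust for those. The omission makes the standard errors mismatch the design only if the same factors stratified allocation, and then the error is on the cautious side. If children were allocated without such strata, the unadjusted test is valid.

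Finally, an article may leave blocking, the child-level sequence and a full covariate list to the full protocol or analysis plan. Their absence is not held against it here.

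All of this stands, and it limits the harm. It does not remove the inconsistency, because the section on allocation is present and leaves its unit unnamed beside a sequence for schools. Nor does it justify making adjustment for school and grade depend on observed imbalance, which is a rule the article itself states.

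**Conclusion.** The Randomization section should be corrected because it runs school sampling and allocation to arms together and leaves the allocated unit undefined, while the Abstract and Study design say children or participants. On the better-supported reading, children are allocated and about 80% power at 175 per group stands. (At the 168 per group left by 20% loss from 420 it is 78.5%, which is a separate matter.)

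The consequence for the analysis is then minor: a standard error about 0.5–5% wider than necessary, and power of 80% where about 80.5–84% was available. This assumes that school and grade explain 1–10% of the outcome variance. The error is in precision, not in false positives.

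The figures for allocated schools (power 55% to 13% for ICC 0 to 0.10, and type I error of about 12–31% at ICC 0.01–0.05) show why the unit must be stated. They are conditional and are not a property of the plan as written.

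**What to change.** 1. **Randomization section.** State that schools are sampled, with district and size as sampling factors, and that consenting children are then individually randomised 1:1. Name any allocation strata, or say that there are none. The wording must record what was actually done.
2. **Statistical analyses section.** Pre-specify school (six-level fixed effect) and grade in every primary and secondary model, whether or not they look unbalanced.
3. **Only if whole schools were allocated.** Restate the 80% power with a justified ICC and the number of schools, and use an analysis that accounts for school.

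**Cost of items 1 and 2:** a few sentences, 5 df for school, and one fewer df than the number of grades. Against 336 to 350 analysed children that is negligible. Recruitment runs through schools and grades, so both should be on record and no new measurement is needed. Item 3 would be a substantial redesign, but it arises only if item 1 shows that schools were the allocated unit.
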